## Annex 3 Interview guide for qualitative study Amharic Version

የቃለ መጠይቅ መመሪያ

1. የመግቢያ ጥያቄዎች

ሀ) በጉባኤያችሁ ውስጥ ስንት ሰዎች አሉ?

ለ) እዚህ ቦታዎ ለምን ያህል ጊዜ ኖረዋል?

ሐ) ከዚህ በፊት የተሾሙት የት ነበር?

መ) በጉባኤያችሁ ውስጥ የእናቶች ጤና አገልግሎት አጠቃቀም ሽፋን ምን እንደሆነ ሀሳብ አላችሁ?

1. ስለ እናቶች ጤና (ኤኤንሲ፣ኤስዲኤስ እና ፒኤንሲ) ጥያቄዎችን ከጉባኤዎ አባላት ይቀበላሉ?

ሀ) ምን አይነት ጥያቄዎች?

- የመጽሐፍ ቅዱስ እና የሌላ ጽሑፍ ትርጓሜ

- የውሳኔ አሰጣጥን በተመለከተ የግል ምክር

-ስለ እናቶች ጤና አገልግሎት አጠቃቀሞች (ኤኤንሲ፣ኤስዲኤስ እና ፒኤንሲ) ጤናማ ያልሆኑ እምነቶች እና ልምዶች

- አዲስ የተወለዱትን ስለመመገብ ጤናማ ያልሆኑ እምነቶች እና ልምዶች

ለ) ከማን እና መቼ?

ሐ) እንደዚህ ያሉትን እንዴት ነው የምትይዘው?

መ) ሌሎች ጥያቄዎች?

1. በጉባኤዎ ውስጥ ባሉ ቤተሰቦች ውስጥ የእናቶች ጤና አገልግሎት አጠቃቀምን በሚመለከት የውሳኔ አሰጣጥ ሂደት ሀሳብ አለዎት? በእርስዎ አስተያየት ምን ምክንያቶች ወሳኝ ናቸው?
2. እርስዎ እራስዎ የእናቶችን ጤና (ኤኤንሲ, ኤስኬዲ እና ፒኤንሲ) ለውይይት ያነሳሉ?

ሀ) በቤት ጉብኝት ወቅት?

ለ) በማረጋገጫ ትምህርት ጊዜ?

ሐ) በስብከት?

መ) ያለበለዚያ) በጉባኤ ወይም በመንፈሳዊ ጉባኤ ላይ

1. በእናቶች ጤና ወይም በሌሎች ርዕሰ ጉዳዮች ላይ ከሌሎች የሃይማኖት መሪዎች ጋር ግንኙነት አለህ?

ሀ) ከራስህ ቤተ እምነት?

ለ) ከሌሎች ቤተ እምነቶች?

ሐ) በመደበኛነት? ወይስ በመንፈሳዊ ጉባኤ ወቅት ብቻ?

1. ስለ እናቶች ጤና (ኤኤንሲ፣ኤስዲኤስ እና ፒኤንሲ) ወይም ሌሎች ርዕሶችን በተመለከተ ከመንግስት ጋር ግንኙነት ነበራችሁ?

ሀ) ከቀበሌ አመራሮች ወይም ከጤና ጽ/ቤት ኃላፊ ጋር?

ለ) ከጤና ኤክስቴንሽን ሠራተኞች ጋር?

ሐ) በመደበኛነት? ወይስ በመንፈሳዊ ጉባኤ ወቅት ብቻ?

1. በምናልባት የግዴታ የእናቶች ጤና (ANC፣ SDS እና PNC) ላይ የእርስዎ አቋም ምንድን ነው?
2. አስፈላጊ ነው ብለው የሚያስቡት ሌላ ነገር አለ እና ስለዚህ ማከል ይፈልጋሉ?

## Key message Amharic Version

**የሥልጠና ቁልፍ መልእክቶች**

**የእናቶች እና አዲስ የተወለደ ህመም እና ሞት ዋና መንስኤዎች እና የሚመከር እርምጃ**

**የእናቶች ሞት ዋና መንስኤዎች**

የደም መፍሰስ (የቅድመ ወሊድ እና የድህረ ወሊድ ደም መፍሰስ)፣ ኤክላምፕሲያ (በአደገኛ ከፍተኛ የደም ግፊት ምክንያት የሚከሰት)፣ የፐርፐራል ሴፕሲስ (ኢንፌክሽን)፣ ረጅም/የታገደ ምጥ እና ደህንነቱ ያልተጠበቀ ፅንስ ማስወረድ::

**አነስተኛ የእናቶች ህመም እና ሞት መንስኤዎች**

የደም ማነስ፣ ሳንባ ነቀርሳ፣ ቴታነስ፣ ኤችአይቪ/ኤድስ፣ የልብና የደም ቧንቧ በሽታ፣ በእርግዝና ወቅት ወባ፣ በእርግዝና ወቅት ከመጠን በላይ ማስታወክ እና የተመጣጠነ ምግብ እጥረት::

**አዲስ የተወለደ በሽታ እና ሞት ዋና መንስኤዎች**

ያለጊዜው መወለድ - ከ 37 ሳምንታት እርግዝና በፊት የተወለደ, ዝቅተኛ ክብደት - ከ 2.5 ኪሎ ግራም ክብደት በታች የተወለደ, ሃይፖሰርሚያ, ኢንፌክሽን እና የወሊድ አስፊክሲያ::

**የሚመከር እርምጃ**

የቅድመ ወሊድ እንክብካቤ ክትትል፣ በሰለጠነ የጤና ባለሙያዎች ማድረስ፣ የቅድመ ወሊድ እንክብካቤ በ24 ሰአት ውስጥ፣ የቤተሰብ ምጣኔ አገልግሎት እና አጠቃላይ የፅንስ ማስወረድ እንክብካቤ (ሲኤሲ)፣ የነፍሰ ጡር ሴቶች ኮንፈረንስ ማካሄድ እና የእናቶች መጠበቂያ ቤቶች (MWHs)::

**የትኩረት የቅድመ ወሊድ እንክብካቤ አካላት-**

ለችግሮች እና ውስብስቦች አስቀድሞ ማወቅ እና ማከም።

ለችግሮች እና ውስብስቦች አስቀድሞ ማወቅ እና ማከም።•ለብዙዎቹ በቅድመ ወሊድ እንክብካቤ ውስጥ አስፈላጊ የሆኑ ተግባራትን ከስር ያሉ ሁኔታዎችን አስቀድሞ መለየት በጣም አስፈላጊ ነው - ለምሳሌ የትውልድ ቂጥኝን መከላከል፣ የደም ማነስን መቆጣጠር እና የወባ ችግሮችን መከላከል።

ውስብስቦችን እና በሽታዎችን መከላከል (የብረት ፎሌት የደም ማነስን ለመከላከል፣ቴታነስ ቶክሳይድ፣በነፍሳት ላይ የሚደረግ ሕክምና የተጣራ አቅርቦት፣በጾታ ግንኙነት የሚተላለፉ ኢንፌክሽኖች እና የኤችአይቪ ምርመራ እና የምክር አገልግሎት)

**የወሊድ ዝግጁነት እና ውስብስብነት ዝግጁነት**

የመውሊድ ዝግጁነት እና ውስብስብነት ዝግጁነት ማለት የሰለጠነ የእናቶች እና አዲስ የተወለዱ አገልግሎቶችን ወቅታዊ ተደራሽነት ለማስተዋወቅ የታለሙ አጠቃላይ ፓኬጆች ማለት ነው።

ነፍሰ ጡር እናቶች እና ቤተሰቦቻቸው ለመውለድ ንቁ ዝግጅት እና ውሳኔን ያበረታታል.

የልደት ዝግጁነት፡- ለመደበኛ ልደት የማቀድ ሂደት ነው:: ውስብስብ ዝግጁነት በድንገተኛ ጊዜ የሚያስፈልጉትን ድርጊቶች አስቀድሞ በመጠባበቅ ላይ ነው።

የአደጋ ጊዜ እቅድ በአደጋ ጊዜ በፍጥነት መከናወን ያለባቸውን ድርጊቶች ሁሉ የመለየት እና የመስማማት ሂደት ነው, እና ዝርዝሮቹ ሁሉም ሰው እንዲረዱት እና አስፈላጊው ዝግጅት ይደረጋል::

**የልደት ዝግጁነት የሚከተሉትን ያጠቃልላል::**

ምርጫዎቿን ማክበር ስለ ደህንነት እና ንጽህና አቅርቦት ሁሉንም አስፈላጊ መረጃዎችን መስጠት አለቦት ነገርግን በመጨረሻ አንዲት ሴት መውለድ የምትፈልግበትን ቦታ እና በወሊድ ጊዜ ከማን ጋር መሆን እንደምትፈልግ መምረጥ አለብህ።

እሷን እና ቤተሰቧን በወሊድ ጊዜ እና በድህረ ወሊድ ጊዜ ውስጥ የድጋፍ ምንጮችን እንድትለይ መርዳት።

ከወሊድ ጋር የተያያዙ ተጨማሪ ወጪዎችን ማቀድ, ለእሷ እንክብካቤ እና አዲስ ለተወለደ ሕፃን እንክብካቤ ቁሳቁሶችን ማዘጋጀት.

**የልደት ዝግጁነት እና ውስብስብ ዝግጁነት አካላት**

ችሎታ ያላቸው የጤና ባለሙያዎች፣ ተቋም ወይም የትውልድ ቦታ፣ መጓጓዣ፣ ፈንዶች፣ ደጋፊ ሰው፣ ውሳኔ ሰጪ እና በወሊድ ላይ ያሉ አደገኛ ምልክቶች::

**በእርግዝና ወቅት አደገኛ ምልክቶች እና በአራስ ሕፃናት ውስጥ አደገኛ ምልክቶች**

የአደጋ ምልክት የእናቲቱን ወይም ያልተወለደውን ልጅ ወይም ሁለቱንም የሚያሰጋ ከባድ ነዉ:፡ በሽታ ነፍሰ ጡር ሴት የአደጋ ምልክት ካላት የአደጋ ምልክቶችን ማወቅ እና ወዲያውኑ እንክብካቤ ማግኘት አለባት።

**ቅድመ ወሊድ አደገኛ ምልክቶች፡** (ከባድ ራስ ምታት፣ የዓይን ብዥታ፣ ገዳይ የሆነ እንቅስቃሴ የለም፣ የደም ግፊት መጨመር፣ የፊት እብጠት፣ የእጆች/እግር እብጠት፣ መናድ፣ ከፍተኛ የሆነ የሴት ብልት ደም መፍሰስ፣ በታችኛው የሆድ ክፍል ውስጥ ከባድ ህመም እና ፈሳሽ መፍሰስ (ሜኮኒየም የቆሸሸ)።

**ምጥ/መውለድ አስጊ ምልክቶች**፡ (ከሴት ብልት ውስጥ ብዙ ደም መፍሰስ፣ መጥፎ ሽታ ያለው ፈሳሽ፣ ከፍተኛ ትኩሳት፣ የሕፃኑ እጅ ወይም እግር መጀመሪያ ይወጣል፣ ሕፃኑ ባልተለመደ ቦታ ላይ ነው፣ ምጥ ማራዘም (12 ሰአታት)፣ የተቀመጠ የእንግዴ ልጅ፣ የማህፀን ስብራት፣ ኮርድ መራባት፣ ገመድ፡፡

**ከወሊድ በኋላ አደገኛ ምልክቶች፡** (ከሴት ብልት ውስጥ ከመጠን በላይ ደም መፍሰስ፣ መጥፎ ሽታ ያለው ፈሳሽ፣ ከፍተኛ ትኩሳት፣ የተገለበጠ የጡት ጫፍ፣ ቴታነስ፣ የቆመ የእንግዴ ቦታ፣ ከባድ የሆድ ህመም፣ መናወጥ እና የተጨማለቀ ጡት/የጡት ማበጥ)፡፡

**ለአራስ ሕፃናት አደገኛ ምልክቶች፡** (በደካማ መመገብ ወይም ማጥባት አለመቻል፣ ተቅማጥ፣ የገመድ አካባቢ መቅላት፣ ቀይ አይን/የሚፈሰሱ አይኖች፣ የመተንፈስ ችግር፣ የቆዳ/ጃንዲስ ቢጫ ቀለም፣ ሃይፖሰርሚያ/ መንቀጥቀጥ፣ በቆዳ ላይ ጉድፍ/ የቆዳ ጉዳት፣ ህጻን አይጎዳም፡፡

ዶክተር ወይም ሌሎች የጤና ባለሙያዎችን ማማከር፡ የአደጋ ምልክቶች ካላቸው (በእርግዝና፣ ምጥ እና ወሊድ፣ ከወሊድ ከ42 ቀናት በኋላ እና አዲስ የተወለደ የአደጋ ምልክቶች) ካለባቸው።

# Key message Hadiyisa Version

**Losa’n horoori asso**

**Amoo’ikaa hareechi qaraamu cilluwwika lehiki horoori maska’uwwaa horaakam googuwwa.**

**Horoori ihaakkko ammaa’nne lehoo eboo luwwi:**

Xiigi dunaamchcha, xiigi gafechchi exximma,jabbinne amadamchcha, xuuchi dassimma lamifoollano amani bee’e gundismma.

**Hoffani ihaakkko ammaa’nne lehoo eboo luwwi;**

- Xiigi hoffe’nna, Suqqo’I jabbo, teetanosa, HIV/AIDS, wodda’nni jabbo, kachchisi jabbo, lamifoollano amannene erisa goxaansimmaa hurbaaxxi hoffe’nna.
- Horoori ihaakko hareecho qaraamukki ciilluwwi xissikkii lehikkii maska’uwwi;
- Saadi lamari saanti afoo’ni qoxxu bee’i ciilluwwi qaramchi, 2.5 kiilograminsi hofaani ihakko ciilluwwi qaraamchi, fooshee’imma hoogimmi, mulli jabbuwwimi lehina mashkka;I ihookko.

**Amoo’ikaa hareechi qaraamu cilluwwika lehoo xissoo hooriminaa baxximmi hassisoo baxxuwwi;**

- Lamifoollani la’aamukkisam qaqissimminne fayya’oommi eegechchi mine marimba, ayya’oommi eegechi bikkina losu manninne qarrimma, abaroosa qoodakka’ a qarimmi awaado awwaxximma, harreechchi ciillichchi qaramukki mati balli woronne fayya’oomi awwado siiximma, Lamifoolluwwi konfiransanne dummichchanne baxxamiimma, qarriimmina guddukki mine awwaaxximma.

**Lamifoollani ammane awwaximmi hassisoo horoori luwwi:**

Lamifoollani ammanenne waroo hawwo gaassaka’a la’immaa awado siixximma

***Awwaaduwoomimi:***

- xiigi hoffechcha ege’llimma, kachchisi jabbiinsi ege’llimma, sifi’lli jabboo li’inni hoffe’nni hawoo eg’llimma.
- Areeni fooleti yakkami xiigi hoffechcha horoo kiniina awwaxximma, tetanoosi qaraare awaaximma, kachchis jabbiinsi egeroo shara’a awwaxxiimma, edaanchinne higoo jabbuwwa HIV gaganne yooda’e la’immi awwado siixximma.
- Cillichchi qaramukkisam qaaqisakka’a anuuna iciisimma odim ciilichchi qramukkaannii lohi again afeebe’e xale’i anuuna iicisimma.
- Hareechchi qaraamu ciilluwwina Awwaadoobe’i hurbaata ittisimma urimmaa hawoodoo ama’nnatinsi gaga qeessimma.
- Lamifoollani ammane orraachchi mucuroomaa egee’llimma
- Qarrimmina hassisso luwwa gudiissimmaa kee’maa’lli hawwi waroota’niimi gudimma
- Gagi faya’ooma erisa egee’llimma

**Qarrimmina hassisso luwwa gudiissimmaa kee’maa’lli hawwi waroota’niimi gudimma**

Kuu guddimmi qaraamoo ciillichchi fayya’oominam ihukkoo ami fayya’omina horemi erisa awwaadookko.

Ku Qarrimmina hassisso luwwa gudiissimmaa amaadoo luwwi:

- Qariimmi bikkina losaakkoo mancho la’imma
- Qarakkam fayaa’oommi egechchi mine la’imma
- Qariimina marakkam amanina tiransporta gudisimma
- Qarammi amane maqire maroo manchoo hara’moo manna la’imma

**Lamifoollani ammanenne hareechchi qaramoo ciilluwwanne siidameena xanoo maree’wwa**

Ku siidameena xanoo maree’wwi amanaamii cillichchinammii foorina badiisoo bikkina ku maree’I siidamulas qaqisimminne fayya’oomi egee’llimmi mine marimmi hasiisookko.

- **Lamifoollani ammanenne he’eena xanoo jabbi mare’uwwi: (**kee’mmaa’li horoo’li damuumi , illi mo’immi hawwi, godaphi woronne yookki ciillichchiki mikimikaati bee’immi, xiigi gafechchi edimma, illi kolli dashshimma, angi te’imi lokki dashshimma, kullulaa’imma, qa’li ma’nninne xiigi firimma, kee’maa’lisa godabi xissimma.
- **Xuuchi amane te’mi qarimmi amane he’eena xanoo hawwi mare’uwwi: (**qa’li ma’nninne xiigi firimma, boboo daaadali luwwi firiimma, orachchi erisa iibbimma, ciiillichchiki angi gasaa qaramchcha, mati ballii lophphaakko xuuchi hee’imma, maqeeri qaraamoo’ni gattimmi, qa’li ma’nni xooqimma.
- **Qarimmi lasage hee’ena xanoo hawwi mare’e:** (qa’li ma’nninne xiigi firimma**,** boboo daaadali luwwi firiimma**,** orachchi erisa iibbimma**,** anuu’ni woroonne aagimma**,** maqeeri qaraamoo’ni gattimmi**,** kee’maa’lisa godabi xissimma**,** kulluulaa’immaa anuuni dashshimmaa)
- **Hareechchi qaraamu ciilluwwanne he’eena xanoo hawwi mare’e: (**anuuna iicimma hoogimma, godabi aadissimma**,** suri kasharimma**,** illi kasharimma**,** foosheechcha hoogimma**,** orachchi baari hagari ihimma**,** huxiisimma**,** orachchonne qoshi firimma**,** cillichchi larubeelas**,** orachchi shokiisimma**,** baqimma hogimma**,** qaqiiso qaqiiso foshee’imma**,** shumi te’mi ciri firimma hoogimma.

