## 4.13 Intervention

For 4 months, trial participants in the intervention group will receive behavioural change communication on maternal health, while those in the control group will receive usual care. In collaboration with HEWs, kebeles leaders and religious leaders, the researcher and field workers will arrange an appropriate training place in the intervention clusters to train sampled pregnant mothers on prenatal health behaviour. During the intervention period, Hadiyisa will be the language of communication (the local language).

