**The focuses of training (intervention key messages) on:**

**Antenatal care:** (taking TT injection, taking Calcium Consumed 100+ IFA tablets , eating more food during pregnancy, eating Green vegetables , eating Fruits during pregnancy , drinking milk during pregnancy , eating pulses and beans during pregnancy , taking nap/rest, regularly during pregnancy, Husband accompanying for ANC (regularly /mostly), Human immunodeficiency virus (**HIV)**  **and syphilis** test, tobacco use and substance use. **Benefits of early and exclusive breastfeeding (**Provides the best nutrition for the new-born Is easily digested and efficiently used by the baby’s body, Protects against infection and other illnesses, Offers some protection against allergies, Is cost-effective and affordable, Promotes mother-baby bonding. **Unhealthy beliefs and practices about feeding new-borns**, **Hygiene during pregnancy**, **Breastfeeding and contraception, Benefits of birth spacing: (**Maternal mortality, fetal death (miscarriage or stillbirth), neonatal mortality, Anaemia in the mother during subsequent pregnancies, Postpartum inflammation of the endometrium lining the uterus, Premature rupture of the amniotic membranes surrounding the fetus, Premature birth, Intrauterine growth retardation and a low birth-weight baby and Malnutrition of new-borns and infants due to insufficient breast-milk**).**

**Prenatal Danger signs: (**Severe headache, Blurred vision, Fatal movement absent, High blood pressure, Edema of the face/swelling, Oedema of the hands/leg swelling, Convulsions, Excessive vaginal bleeding, Severe lower abdominal pain and Leaking fluid (meconium stained).

**Labor/delivery** **Danger signs: (**Excessive vaginal bleeding, Foul-smelling discharge, High fever, Baby’s hand or feet coming out first, Baby is in abnormal position, Prolong labor (.12 hours), Retained placenta, Rupture uterus, Cord prolapse, Cord around neck and Convulsion).

**Postpartum Danger signs:** (Excessive vaginal bleeding**,** Foul-smelling discharge**,** High fever**,** Inverted nipples**,** Tetanus**,** Retained placenta**,** severe abdominal pain**,** Convulsions **and** Engorged breasts/swelling of breasts)

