**Part V Knowledge of obstetric danger signs**

| **Sir. No.** | **Questions** | | **Responses** | **Skip to** |
| --- | --- | --- | --- | --- |
| 501 | In your opinion, can unforeseen problems related to pregnancy occur during any pregnancy or childbirth that could endanger the life of a woman? | | 1. Yes 2. No 3. I don’t know |  |
| 502 | In your opinion, what are some serious | | 1. Bleeding , 1. Yes, 2. No 2. Severe headache, 1. Yes, 2. No 3. Blurred vision,1. Yes, 2. No 4. Convulsions, 1. Yes, 2. No 5. Swollen hands/face, 1. Yes, 2. No 6. High fever, 1. Yes, 2. No 7. Loss of consciousness, 1. Yes, 2. No 8. Difficulty breathing, 1. Yes, 2. No 9. Severe weakness , 1. Yes, 2. No 10. Severe abdominal pain, 1. Yes, 2. No 11. Accelerated/ reduced, 1. Yes, 2. No 12. Fetal movement, 1. Yes, 2. No 13. Water breaks without labor, 1. Yes, 2. No 14. other specify 15. None 16. I don’t know |  |
| 503 | In your opinion, what are some serious health problems that can occur during labor and childbirth that could endanger the life of a pregnant woman?  PROBE: Any others? | | 1. Severe bleeding, 1. Yes, 2. no 2. Severe headache, 1. Yes, 2. no 3. Convulsions, 1. Yes, 2. no 4. High fever, 1. Yes, 2. no 5. Loss of consciousness, 1. Yes, 2. no 6. Labor lasting >12 hours, 1. Yes, 2. no 7. Placenta not delivered 30 minutes after baby, 1. Yes, 2. no 8. other___ (specify) 9. none 10. don’t know |  |
| 504 | In your opinion, could a woman die from [this problem] any of these problems? | 1. Yes 2. No | |  |
| 505 | In your opinion, what are some serious health problems that can occur during the first 2 days after birth that could endanger the life of the woman?  PROBE: Any others? | 1. Difficult or fast breathing, 1. Yes, 2. No 2. Yellow skin/eye color (jaundice), 1. Yes, 2. No 3. Poor sucking or feeding, 1. Yes, 2. No 4. Pus, bleeding, or discharge from around the umbilical cord, 1. Yes, 2. No 5. Baby very small, 1. Yes, 2. No 6. Skin lesions or blisters, 1. Yes, 2. No 7. Convulsions/spasms/ rigidity, 1. Yes, 2. No 8. Lethargy/ unconsciousness, 1. Yes, 2. No 9. Red or swollen eyes with pus, 1. Yes, 2. No 10. other (specify)____________ 11. none | |  |
| **506** | In your opinion, could a newborn baby die from [this problem] any of these  Problems? | 1. Yes 2. No 3. I don’t know | |  |

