| 324 | የመጨረሻ ልጅህን የት ነው የወለድከው? | 1. ቤት  2. ሆስፒታል  3. ጤና ጣቢያ  4. ጤና ጣቢያ ሌላ ይግለጹ_________ |  |
| 325 | በእርግዝና ወቅት አጨስ ወይም ለሁለተኛ እጅ ማጨስ ተጋልጧል? | 1. አዎ 2. አይደለም |  |
| 326 | በእርግዝና ወቅት ለፀረ-ተባይ ወይም ለሌሎች መርዛማ ኬሚካሎች ተጋልጠዋል? | 1. አዎ 2. አይደለም |  |
| 327 | በእርግዝና ወቅት ለኤክስሬይ ወይም ለሌሎች ለሕክምና ያልሆኑ ራዲዮሎጂካል ንጥረ ነገሮች ተጋልጠዋል? | 1. አዎ 2. አይደለም |  |
| 328 | በእርግዝና ወቅት ፎሊክ አሲድ ወስደዋል? | 1. አዎ 2. አይደለም |  |
| 329 | በእርግዝና ወቅት አልኮል ጠጥተዋል? | 1. አዎ 2. አይደለም |  |

ክፍል IV የልደት ዝግጁነት እና ውስብስብነት ዝግጁነት

| **Sir. No.** | **ጥያቄዎች** | **ምላሾች** | **Skip to** |
| --- | --- | --- | --- |
| 401 | "የልደት ዝግጁነት" የሚለውን ቃል ሰምተህ ታውቃለህ? | 1. አዎ  2. አይደለም  3. አላስታውስም |  |
| 402 | በእርስዎ አስተያየት አንዲት ሴት ለመውለድ ለማዘጋጀት ምን ማድረግ ትችላለች? | 1) የመጓጓዣ ሁነታን መለየት,  1. አዎ 2. አይደለም   1. ገንዘብ ይቆጥቡ, 2. አዎ 2. አይደለም   3) ደም ለጋሾችን መለየት  1. አዎ 2. አይደለም  4) የሰለጠነ የወሊድ ረዳትን መለየት  1. አዎ 2. አይደለም   1. ደጋፊ ሰው   1. አዎ 2. አይደለም   1. ሌሎች ይግለጹ |  |
| 404 | የእርስዎ ማህበረሰብ ሴቶች ለመውለድ በሚዘጋጁበት ጊዜ ለመርዳት አገልግሎት ይሰጣል? ለምሳሌ፣ አሉ፡- | 1) የመጓጓዣ ሁነታን መለየት,  1. አዎ 2. አይደለም   1. ገንዘብ ይቆጥቡ, 2. አዎ 2. አይደለም   3) ደም ለጋሾችን መለየት  1. አዎ 2. አይደለም  4) የሰለጠነ የወሊድ ረዳትን መለየት  1. አዎ 2. አይደለም   1. ደጋፊ ሰው 2. አዎ 2. አይደለም 3. ሌሎች ይግለጹ |  |

ክፍል V በእርግዝና, በምጥ እና በወሊድ ጊዜ, አዲስ የተወለደ እና የድህረ ወሊድ ጊዜ አደገኛ ምልክቶችን ማወቅ

| **Sir. No.** | **ጥያቄዎች** | | **ምላሾች** | **Skip to** |
| --- | --- | --- | --- | --- |
| 501 | በእርስዎ አስተያየት ከእርግዝና ጋር የተያያዙ ያልተጠበቁ ችግሮች በማንኛውም እርግዝና ወይም ልጅ መውለድ የሴቶችን ሕይወት አደጋ ላይ ሊጥሉ ይችላሉ? | | 1. አዎ  2. አይደለም  3. አላስታውስም |  |
| 502 | በእርስዎ አስተያየት አንዳንድ ከባድ ችግሮች ምንድናቸው? | | 1. የደም መፍሰስ   1. አዎ 2. አይደለም   1. ከባድ ራስ ምታት   1. አዎ 2. አይደለም   1. የደበዘዘ እይታ   1. አዎ 2. አይደለም   1. መንቀጥቀጥ   1. አዎ 2. አይደለም   1. እብጠት እጆች / ፊት   1. አዎ 2. አይደለም   1. ከፍተኛ ትኩሳት   1. አዎ 2. አይደለም   1. የንቃተ ህሊና ማጣት   1. አዎ 2. አይደለም   1. የመተንፈስ ችግር   1. አዎ 2. አይደለም   1. ከባድ ድክመት   1. አዎ 2. አይደለም   1. ከባድ የሆድ ህመም   1. አዎ 2. አይደለም   1. የተፋጠነ / የተቀነሰ የፅንስ እንቅስቃሴ   1. አዎ 2. አይደለም   1. Water breaks without labor   1. አዎ 2. አይደለም   1. ሌሎች ይግለጹ 2. የለም 3. አላውቅም |  |
| 503 | በእርስዎ አስተያየት፣ ነፍሰ ጡር ሴትን ህይወት አደጋ ላይ የሚጥሉ ምጥ እና በወሊድ ወቅት ሊከሰቱ የሚችሉ ከባድ የጤና ችግሮች ምን ምን ናቸው?  PROBE: ሌላስ? | | 1. የደም መፍሰስ   1. አዎ 2. አይደለም   1. ከባድ ራስ ምታት   1. አዎ 2. አይደለም   1. መንቀጥቀጥ   1. አዎ 2. አይደለም   1. ከፍተኛ ትኩሳት   1. አዎ 2. አይደለም   1. የንቃተ ህሊና ማጣት   1. አዎ 2. አይደለም   1. Labor የሚቆይ>12 ሰዓታት   1. አዎ 2. አይደለም   1. Placenta ከተወለደ ከ 30 ደቂቃዎች በኋላ አልተወለደም   1. አዎ 2. አይደለም   1. ሌሎች ይግለጹ 2. የለም 3. አላውቅም |  |
| 504 | በእርስዎ አስተያየት አንዲት ሴት ከእነዚህ ችግሮች ውስጥ በአንዱ ልትሞት ትችላለች? | 1. አዎ 2. አይደለም 3. አላውቅም | |  |

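### The Hadiyisa key-message sheet appears to put prolonged labour at more than one day, where the English and Amharic messages and the questionnaire say 12 hours

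*Protocol*

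**What the plan says.** **Prolonged labour.** The English key messages in section 4.13 list "Prolong labor (.12 hours" among the labour and delivery danger signs; the stray full stop is probably a damaged greater-than sign. The Amharic key messages have "ምጥ ማራዘም (12 ሰአታት", also 12 hours. Item 503 of the questionnaire codes "Labor lasting >12 hours" in English (Annex 1, Part V) and "Labor የሚቆይ>12 ሰዓታት" in the Amharic version (Annex 2). The labour list in the Hadiyisa key messages has "mati ballii lophphaakko xuuchi" and no 12-hour figure.

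**Language of delivery.** Section 4.13 states that "Hadiyisa will be the language of communication". The subsection on group training by religious leaders adds that the manual and posters are produced in the local language.

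**The 24-hour contact.** The Amharic list of recommended actions has "የቅድመ ወሊድ እንክብካቤ በ24 ሰአት ውስጥ", which names antenatal care within 24 hours. The corresponding Hadiyisa list has "qaramukki mati balli woronne", a contact within one day of the newborn's birth. The postnatal care paragraph in Chapter One places the first postnatal contact within 24 hours of birth.

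**Checks on wording.** Section 4.18 describes translation and back-translation for the questionnaire only. The text on the central route of persuasion, before section 4.16, requires the information discussed to be accurate and consistent.

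**The concern.** The danger-sign lists tell a woman what should make her seek care, and the Amharic sheet says that a woman with a danger sign should get care immediately. A duration attached to a danger sign therefore works as a trigger for action. If the sheet in the teaching language carries a different duration from the other versions, the intervention content is not defined consistently on a point that bears on the safety of women in labour.

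Fidelity monitoring is also affected. An observer is to rate sessions for accuracy and complete content, but for this item the protocol offers two reference texts that disagree. The trial would also teach one duration while printing another on the form used for Objective 1, although the consequence for scoring is limited.

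**Working it through.** No sample size, power or error-rate figure is involved. The check is a side-by-side comparison, with one ratio at the end.

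**Step 1: duration given in each version.**

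| Version | Duration |
| --- | --- |
| English key messages, section 4.13 | 12 hours |
| Amharic key messages | 12 hours |
| Item 503, English | more than 12 hours |
| Item 503, Amharic | more than 12 hours |
| Hadiyisa key messages | *mati ballii*; no figure in hours |

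**Step 2: is the Hadiyisa entry the same danger sign?** Its position says so. In the English list, prolonged labour comes after the entries on the baby's hand or feet coming first and abnormal position, and directly before retained placenta. The Hadiyisa entry sits between the hand coming first and the entry *maqeeri qaraamoo'ni gattimmi*. That last entry recurs in the Hadiyisa postpartum list, between inverted nipples and severe abdominal pain, where the English postpartum list has tetanus and retained placenta. It is therefore retained placenta. The word *xuuchi* also stands in the heading of the Hadiyisa labour list and among its main causes of maternal death, where the Amharic counterpart has prolonged or obstructed labour.

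**Step 3: what does *mati balli* mean?** The recommended-action lists in the two local languages run closely parallel, though not in identical order. Each contains one entry with a time limit. The Amharic one says within 24 hours; the Hadiyisa one says *mati balli woronne*. This supports reading *mati balli* as one day.

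**Step 4: what cannot be checked.** The word *lophphaakko*, read here as exceeding, occurs once and has no parallel in the document. The conflict does not depend on it, because the only time unit in the entry is *mati ballii*. Whether the phrase means more than a day, rather than about a day, does depend on it.

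**Step 5: size.** With *mati balli* = 24 hours, the ratio is 24/12 = 2.

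**Step 6: effect on the score.** Section 4.16 counts correct spontaneous mentions. Item 503 has seven named codes (severe bleeding, severe headache, convulsions, high fever, loss of consciousness, prolonged labour, undelivered placenta), so one of seven is touched. An answer of more than 24 hours is necessarily more than 12 hours, so it falls inside the printed code.

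**Step 7: the 24-hour contact.**

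| Place | Time | Service |
| --- | --- | --- |
| Chapter One, postnatal care | 24 hours | first postnatal contact |
| Amharic recommended actions | 24 hours | antenatal care |
| Hadiyisa recommended actions | one day | health care after the newborn's birth |

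The time agrees in all three; the service does not. The Amharic list has already named antenatal follow-up, and this entry follows skilled delivery, which suggests a slip in the noun.

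**The case against.** The strongest reply is that this is a possible translation slip in one annex phrase, read without a glossary. The support for *mati balli* comes from pairing two lists that themselves disagree on the service named, and the key verb is uncorroborated. The manual and posters that leaders will actually use are not in the document, the intervention is to be pretested, and sampled sessions are rated for accuracy. The primary sample-size outcome, skilled delivery, is not scored from this item.

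Much of this stands. The translation needs a qualified reader, and the annex does not prove what will be said in a session. But the two lists disagree on the service, not on the time, so they can still serve to match the time phrase. Pretesting and session ratings are not described as comparing the language versions. And whatever the Hadiyisa phrase means exactly, it does not state 12 hours.

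Three stronger inferences are tempting and are not supported:

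- *That women taught from the Hadiyisa sheet would have no code to match.* Labour beyond a day meets the 12-hour code, and no passage requires a woman to state a duration. No bias in Objective 1 is shown.
- *That different leaders will teach different durations.* No passage has leaders teaching from the Amharic sheet; the stated language is Hadiyisa.
- *That a second time limit differs.* The 24-hour figure is the same throughout; only the service attached to it changes.

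**Conclusion.** The inconsistency is real and should be resolved before the intervention starts. Four places give 12 hours for prolonged labour, and the sheet in the language of the intervention appears to give more than one day, twice as long if *mati balli* is 24 hours. That size rests on parallel text within the protocol and on one word that needs a translator's confirmation. Its importance lies in the safety content given to pregnant women. The effect on the knowledge score is probably small, and nothing here touches randomisation, sample size or the analysis model. The mismatch over the 24-hour contact is a separate and lesser error in the service named. The documents do not settle which labour duration is intended, and this point takes no position on it.

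**What to change.** 1. Have a qualified Hadiyisa translator confirm the prolonged-labour phrase.
2. Reconcile the duration across the English key messages in section 4.13, the Amharic and Hadiyisa key messages, and item 503 in both questionnaires. The clinical co-investigators should decide the wording, so that what is taught and what is printed on the form agree.
3. Reconcile the service attached to the 24-hour contact across Chapter One and the Amharic and Hadiyisa recommended-action lists.
4. Extend the back-translation in section 4.18 to both local-language message sheets, and check the manual and posters against the agreed text.

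The cost is a few corrected lines, a translator's check and back-translation of two short sheets. It should be done before leaders are trained and posters printed, because distributed posters cannot easily be recalled.
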